This study aims to evaluate the clinical effects of exogenous albumin infusion compared to 0.9% saline. The primary objective is to assess the efficacy of albumin infusion in reducing the severity and incidence of PPCs. The secondary objectives include evaluating the duration of postoperative invasive mechanical ventilation, the incidence of postoperative acute kidney injury (AKI), the occurrence of postoperative cardiovascular complications, the length of ICU stay, the total length of hospital stay, all-cause postoperative mortality, and changes in T-cell subsets as measured by flow cytometry. By comprehensively analyzing pulmonary, renal, cardiovascular, and hospitalization-related outcomes, this study aims to systematically assess the clinical value of albumin infusion in perioperative management.

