**Sample size**

Based on the published literature,^13,14^ and the results of the pre-test, we estimated that the difference in postoperative pulmonary complications scores between the intervention and control groups would be 0.3, with a standard deviation of 0.45. For postoperative pulmonary complications incidence, we assumed a rate of 60% in the control group and anticipated a 50% relative reduction in the intervention group. Using a two-sided test with a significance level (α) of 0.05 and a power of 80%, the required sample size was calculated separately for each outcome. The sample size estimation based on postoperative pulmonary complications scores resulted in a requirement of 74 patients, whereas the calculation based on postoperative pulmonary complications incidence indicated a requirement of 58 patients. To ensure sufficient statistical power, the larger sample size of 74 was adopted. Accounting for a dropout rate of 5%, the final recruitment target was set at 80 patients.

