For flow cytometry measurements at different time points, Mauchly’s test will be conducted to assess the assumption of sphericity. If the assumption is met, repeated-measures analysis of variance (repeated-measures ANOVA) will be used, followed by Bonferroni post hoc correction for multiple comparisons. If the assumption is violated, Greenhouse-Geisser correction or the Friedman test (for non-normally distributed data) will be applied. Additionally, the correlation between changes in T-cell subset counts and PPC scores will be analyzed using Spearman’s rank correlation test; Pearson’s correlation analysis will be used if the data are normally distributed. All statistical analyses will be conducted using two-sided tests, with a P-value <0.05 considered statistically significant. For multiple comparisons, P-values will be adjusted using Bonferroni correction. Data processing and visualization will be performed using SPSS 26.0 (IBM, Armonk, NY, USA), Origin (OriginLab Corporation, Northampton, MA, USA), GraphPad Prism (GraphPad Software, San Diego, CA, USA), and R 4.4.0.

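### The planned correlation of T-cell change with PPC score takes no account of randomised arm, so a treatment effect on both variables would by itself produce a modest pooled correlation

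*Protocol*

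**What the plan says.** The flow cytometry paragraph of the Statistical Analysis section states that "the correlation between changes in T-cell subset counts and PPC scores will be analyzed" by Spearman's test, and that "Pearson’s correlation analysis will be used if the data are normally distributed". It sets the level for its tests: "All statistical analyses will be conducted using two-sided tests, with a P-value <0.05 considered statistically significant". Bonferroni adjustment is named for multiple comparisons, but the family is not defined. The paragraph names no term for arm, no within-arm correlation and no partial correlation, and no other section adds one.

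Three other places bear on this:

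- The objectives at the end of the Background section include "changes in T-cell subsets as measured by flow cytometry" among the secondary objectives of the albumin versus saline comparison. The list of secondary endpoints under Study Endpoints includes neither T-cell change nor its correlation with the score.
- The section on blood sampling and flow cytometry names six cell populations and three sampling times: one before the infusion and two after it (end of surgery and 24 hours). Only patients who consent to this sampling contribute.
- The Sample size section plans for an effect of albumin on the PPC score: a difference that "would be 0.3, with a standard deviation of 0.45".

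**The concern.** The T-cell change is measured after randomisation, and so is the PPC score. The trial is powered for an effect of albumin on the score and also looks for an effect on T cells. If both effects occur, arm is a common cause of the two variables. Albumin patients cluster in one corner of the scatter plot and saline patients in the other, and the combined cloud slopes even if each arm's own cloud is flat.

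The planned test cannot tell that situation from one in which patients with larger T-cell changes have better or worse lungs within the same arm. The ambiguity arises when the trial succeeds on both variables, which is also when a mechanistic reading is most tempting. What is at stake is the interpretation of this one supporting result.

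**Working it through.** **Inputs from the protocol.** Score difference 0.3 and SD 0.45 (Sample size); PPC incidence 60% falling by half to 30% (Sample size); 1:1 allocation (Randomization); target 80 with 5% dropout, so 80 × 0.95 = 76; two-sided 0.05; six cell populations.

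**Assumptions.** The T-cell shift between arms, in SD units, because the protocol gives none: range 0 to 1.0. A consenting subset of 40, because its size is not stated. A Bonferroni family of six. Cut-points that turn a latent normal variable into a 0-5 score.

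**Step 1: the protocol's own figure.** The standardised score effect is 0.3/0.45 = 0.667. The normal formula gives 2 × (1.960 + 0.842)² × 0.45²/0.3² = 35.3, so 36 per arm. The t-based calculation gives 36.3, so 37 per arm and 74 in total, which matches the stated 74. The score effect used below is therefore the one the trial was sized on. The incidence assumption, "we assumed a rate of 60% in the control group and anticipated a 50% relative reduction in the intervention group", implies a latent shift of 0.253 + 0.524 = 0.78 SD. The range for the score shift is thus 0.67-0.78 SD.

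**Step 2: the induced correlation.** With zero correlation inside each arm, 1:1 allocation, and shifts d1 (score) and d2 (T cells), the pooled correlation has absolute size

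|r| = (d1·d2/4) / √[(1 + d1²/4)(1 + d2²/4)].

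For d1 = 0.667 and d2 = 1.0 this is 0.1667 / √(1.111 × 1.25) = 0.141. For d1 = 0.78 and d2 = 1.0 it is 0.195 / √(1.152 × 1.25) = 0.16.

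**Step 3: how often the test rejects.** Simulation with normal data, zero within-arm correlation, d1 = 0.667 and 10,000 runs per row:

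| T-cell shift (SD) | Pooled abs. r (formula) | Pooled Spearman, N=80, 0.05 | Pooled Spearman, N=40, 0.05 | Pooled Spearman, N=80, 0.05/6 | Ranks centred by arm, N=80, 0.05 |
|---|---|---|---|---|---|
| 0 | 0 | 4.9% | 4.8% | 0.7% | 5.0% |
| 0.2 | 0.03 | 5.7% | 5.1% | 1.0% | 4.5% |
| 0.5 | 0.08 | 9.7% | 6.8% | 2.2% | 4.7% |
| 0.667 | 0.10 | 13.9% | 9.3% | 3.4% | 5.1% |
| 1.0 | 0.14 | 23.7% | 14.4% | 8.5% | 4.7% |

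Hand check of the last row at N = 80: Fisher's z is 0.142 × √77 = 1.25, and P(Z > 1.96 − 1.25) is about 24%, as simulated.

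**Step 4: a six-level score.** With the score cut to 0-5 and a score shift of 0.67-0.78 SD, mean absolute r is about 0.03 at a T-cell shift of 0.2 SD and 0.07-0.16 at 0.5-1.0 SD. At nominal 5%, the pooled test rejects in about 5-6% at 0.2 SD. At 0.5-1.0 SD it rejects in 9-28% with N = 76 and 8-16% with N = 40. At 0.05/6 = 0.83% the corresponding rates are 2-10% and 2-5%. Centring ranks within arm returns the nominal 5% test to about 5%. Separate runs differ by about one percentage point at the ends of these ranges.

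**Step 5: only one variable affected.** With no effect on the score and a T-cell shift of 0.8 SD at N = 80, the pooled test rejects in 4.95%. The artefact needs an effect on both variables.

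**The case against.** The strongest reply is that pooling is inferred from silence, and that adjustment of a supporting correlation is commonly left to the SAP, which was not available here. It stands in part: the word pooled is absent, and an SAP could repair the matter. But the protocol itself names the two variables, the coefficients and the level. An analyst following that text would run an unadjusted two-variable test.

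A reader might infer that the planned test is invalid or that its rejections are false positives. The documents do not support that. If albumin moves both variables, the marginal correlation is truly non-zero, and rejecting the null of no correlation is correct. The rejections mislead only about the within-arm question, which the protocol does not state as its null. Nor does the protocol claim mediation.

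A reader might also treat the correlation as a secondary endpoint. The objectives list T-cell changes, not their correlation with the score, and the endpoint list contains neither. The trial calls itself a pilot.

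The Pearson option might look like a second fault, since the score is an ordinal grade. It is nearly moot: Pearson applies only to normal data, and Shapiro-Wilk, one of the two normality tests that the protocol names, rejected normality of the simulated six-level score in every replicate checked.

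Finally, the size depends on an assumed T-cell shift. That objection stands, which is why the small-shift and Bonferroni figures are shown.

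**Conclusion.** The point holds as a limit on interpretation. As written, the plan lets a treatment effect on both variables create a correlation between T-cell change and PPC score, so a significant result could not be taken as an immune link beyond the treatment effect.

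The effect is small to moderate. At its largest in the range examined, |r| of 0.16 corresponds to 0.16² = 2.6% of rank variance. It is negligible at a T-cell shift of 0.2 SD and absent when albumin affects only one of the two variables. Bonferroni over six populations lowers the rejection rate but leaves it above its own 0.83% level for shifts of 0.5-1.0 SD.

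These figures rest on the protocol's score effect and on assumed values for the T-cell shift, the consenting subset, the Bonferroni family and the score cut-points. The primary endpoints, the sample size and the comparison between arms are not affected. This is a desirable improvement, not a necessary correction.

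**What to change.** In the flow cytometry paragraph of the Statistical Analysis section, replace the correlation sentence with Spearman's partial correlation between T-cell change and PPC score adjusted for randomised arm (ranks centred within arm), and report the two within-arm correlations beside it. The choice between Spearman and Pearson then falls away.

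The cost is one sentence of text and one degree of freedom, with no new data and no further patients. The adjusted correlation would still not establish mediation, but it would answer whether the two variables move together among patients given the same treatment.

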**Blood Sample Collection and Flow Cytometry Analysis**

Arterial blood samples were collected from patients who provided informed consent for blood sampling and flow cytometry analysis at three time points: preoperatively, at the end of surgery, and 24 hours postoperatively. Blood sampling was performed via an arterial catheter, specifically before the infusion of albumin or saline, at the completion of surgery, and 24 hours postoperatively, to analyze the dynamics of Th1, Th17, Treg, γδ1, γδ17, and γδTreg cell populations.

During the experimental process, whole blood samples underwent erythrocyte lysis to remove red blood cells, thereby optimizing leukocyte isolation efficiency and minimizing interference from non-target cells. The isolated leukocytes were then subjected to sequential processing, including cell stimulation, viability staining, surface staining, and intracellular staining, ensuring the precise identification of different T cell subsets. Following staining, the cells were washed twice with PBS to remove unbound antibodies and dyes, and subsequently resuspended in PBS to preserve cell viability and signal stability. Data acquisition was performed using a FACS Fortessa flow cytometer (BD, San Diego, CA, USA) to ensure high-throughput detection accuracy and reproducibility.

The study utilized a comprehensive panel of antibodies targeting T cell subsets and cytokines, including APC-H7-CD3, BV605-CD4, BV421-TCRγδ, APC-IL-17A, BV510-IFN-γ, PE-Foxp3, PE-CY7-TGF-β1, BB700-IL-10, and isotype-matched control IgG. All antibodies were purchased from BD PharMingen or BioLegend (San Diego, CA, USA). The selection of antibodies was based on validated literature evidence to ensure specificity and sensitivity of the experimental results.

Flow cytometry data were analyzed using FlowJo software (BD, San Diego, CA, USA), employing a standardized gating strategy to ensure data accuracy, consistency, and reproducibility. To minimize potential bias during analysis, all flow cytometry data underwent independent quality control by at least two researchers, thereby enhancing scientific rigor and reliability.

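### The flow-cytometry analysis fixes single-step Bonferroni; Holm's step-down procedure gives the same familywise guarantee, never rejects less, and is an optional cheap improvement

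*Protocol*

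**What the plan says.** The flow-cytometry paragraph of Statistical Analysis names Bonferroni twice. The repeated-measures ANOVA is to be "followed by Bonferroni post hoc correction for multiple comparisons", and a later sentence extends this to the rest of the T-cell analysis: "For multiple comparisons, P-values will be adjusted using Bonferroni correction". The test level is given as "with a P-value <0.05 considered statistically significant", and the tests are two-sided. No step-down or other sequential method is mentioned.

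The Blood Sample Collection and Flow Cytometry Analysis section sets the scope. Samples are taken "at three time points: preoperatively, at the end of surgery, and 24 hours postoperatively", in patients who agreed to this sampling, "to analyze the dynamics of Th1, Th17, Treg, γδ1, γδ17, and γδTreg cell populations". Statistical Analysis adds correlations between T-cell changes and the PPC score. The objectives, stated at the end of Background, list "changes in T-cell subsets as measured by flow cytometry" among the secondary objectives. T-cell change does not appear in the list of secondary endpoints and plays no part in the Sample size section.

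**The concern.** Bonferroni compares every P-value in a family of m tests with 0.05/m. Holm orders the P-values and compares the smallest with 0.05/m, the next with 0.05/(m−1), and so on up to 0.05, stopping at the first failure. Every Holm threshold is at least as large as the Bonferroni one, and the familywise guarantee is the same whatever the correlation between tests. As a rule for deciding which hypotheses to reject, Bonferroni therefore gives up power and gains no stronger familywise guarantee in return.

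The T-cell data come from a consenting subset of a trial that plans to recruit 80 patients, and that number was set on PPC outcomes. The aim is to describe a pattern across related cell populations, where several real changes are plausible. A step-down method helps most in that situation. What is at stake is how many real subset changes are declared, not whether the error rate is controlled.

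**Working it through.** The protocol states no power, family size or effect for the T-cell tests, so there is no figure of its own to reproduce.

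**Inputs from the protocol:** two-sided level 0.05; six subsets; three time points, hence 3 pairwise contrasts per subset and 6 × 3 = 18 in all.

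**Assumptions:** family size m = 3 (contrasts within one subset), 6 (one test per subset) or 18 (all contrasts); each real effect gives a z-statistic with mean 2.8; correlation between tests 0 or 0.5. The mean of 2.8 corresponds to unadjusted power Φ(2.8 − 1.96) = Φ(0.84) = 80%.

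**Step 1: Bonferroni is valid.** For independent tests with no real effects, familywise error is 1 − (1 − 0.05/m)^m: 0.0492 (m = 3), 0.0490 (m = 6), 0.0488 (m = 18).

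**Step 2: thresholds.** For m = 3, Bonferroni uses 0.0167 throughout; Holm uses 0.0167, 0.025, 0.05. For m = 6, Bonferroni uses 0.0083 throughout; Holm uses 0.0083, 0.01, 0.0125, 0.0167, 0.025, 0.05.

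**Step 3: Bonferroni power in closed form.** Power per real effect is Φ(2.8 − z), with z the two-sided critical value at 0.05/m:
- m = 3: Φ(2.8 − 2.394) = 65.8%
- m = 6: Φ(2.8 − 2.638) = 56.4%
- m = 18: Φ(2.8 − 2.991) = 42.4%

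**Step 4: Bonferroni against Holm by simulation** (100,000 replicates per scenario; independent tests shown).

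| m | real effects | average power, Bonferroni | average power, Holm | gain (points) | familywise error, Bonferroni → Holm |
|---|---|---|---|---|---|
| 3 | 1 | 65.9% | 66.1% | 0.2 | 0.0328 → 0.0440 |
| 3 | 2 | 65.8% | 69.5% | 3.7 | 0.0169 → 0.0372 |
| 3 | 3 | 65.8% | 75.0% | 9.2 | no true nulls |
| 6 | 1 | 56.3% | 56.4% | 0.1 | 0.0421 → 0.0466 |
| 6 | 3 | 56.4% | 59.5% | 3.1 | 0.0237 → 0.0348 |
| 6 | 6 | 56.4% | 68.1% | 11.7 | no true nulls |
| 18 | 1 | 42.6% | 42.7% | 0.1 | 0.0455 → 0.0465 |
| 18 | 9 | 42.5% | 45.3% | 2.8 | 0.0246 → 0.0322 |
| 18 | 18 | 42.4% | 51.1% | 8.7 | no true nulls |

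The simulated Bonferroni powers agree with step 3. With correlation 0.5 and all effects real, the gains are 7.7 points (m = 3: 65.8% to 73.5%), 10.4 (m = 6: 56.4% to 66.8%) and 10.4 (m = 18: 42.5% to 52.9%). With no real effects the two methods have identical familywise error: 0.0496, 0.0499 and 0.0486 for m = 3, 6 and 18 with independent tests. In no replicate did Bonferroni reject a hypothesis that Holm kept.

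**Step 5: where the gain lies.** Both methods need the smallest P-value to be at or below 0.05/m before anything is rejected, so the chance of any rejection is the same by construction. In the simulation, the chance of at least one true rejection differed by no more than about 0.2 point (m = 6, all real: 99.3% for both). The gain is in second and later rejections. With all six of six effects real, the chance of finding all six rises from 3.2% to 21.8% (independent) or from 19.1% to 43.9% (correlation 0.5).

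**The case against.** The strongest reply is that nothing here is wrong. Bonferroni is valid, pre-specified and conservative; it creates no bias, no inflated error and no contradiction. It also has two properties that Holm lacks: it bounds the expected number of false rejections at 0.05, and it gives simple simultaneous confidence intervals that match its tests. Holm's extra rejections are not free either, since realised familywise error moves up within the guarantee (0.0169 to 0.0372 with two of three effects real). All of this stands, and it is why the point is an optional improvement and not a correction.

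A further objection is that the protocol does not say whether the family is one subset's contrasts, the six subsets, or all tests together. That is true, and it limits what can be said about size. It does not affect the comparison, because Holm is at least as powerful as Bonferroni on any family.

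A reader might infer more than the protocol supports:
- *That Bonferroni would make the trial miss a T-cell signal altogether.* It would not; the chance of at least one rejection is essentially the same.
- *That the gain is large in general.* The rise from 3.2% to 21.8% needs all six subsets truly changed, each with 80% unadjusted power. With one real effect the gain is about 0.1 to 0.2 point.
- *That Holm's familywise error stays well under 5%.* With no real effect, or only one, it reaches about 4.4% to 5.0% with independent tests.
- *That a between-arm T-cell comparison is affected.* The flow-cytometry paragraph describes analysis over time points and correlations with the PPC score; it spells out no between-arm T-cell test.

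**Conclusion.** The point holds as an optional, cheap improvement. The protocol fixes single-step Bonferroni in two sentences. Holm gives the same 0.05 familywise guarantee under any dependence, never rejects less, and can reject more when two or more effects are real. That ordering is a property of the procedures and rests on no assumption about this trial.

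The size does rest on assumptions: 80% unadjusted power per real effect and families of 3, 6 or 18 tests. On these, the gain in average power runs from about 0 points (one real effect) to 9 to 12 points (all real, 3 or 6 independent tests), or 8 to 10 points for the same families with correlation 0.5. Familywise error stays at or below 5% in every scenario. The analysis is supportive, and neither the primary PPC endpoints nor the sample size is touched. It would be wrong to read this as an error in the plan.

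**What to change.** In the flow-cytometry paragraph of Statistical Analysis, replace Bonferroni with Holm's step-down correction in both sentences: the one on post hoc contrasts after the repeated-measures analysis and the general one on multiple comparisons. Apply it to the same family of tests, covering the post hoc contrasts and the correlations with the PPC score. Make the change before any T-cell result is seen, because a later switch to a method that can only add rejections would look data-driven.

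The cost is small. No extra data, patients or software are needed; Holm adjustment is a standard function in R, which that paragraph already lists. Simple simultaneous confidence intervals are lost, so unadjusted intervals would be reported beside Holm-adjusted P-values and labelled as such, since the two can disagree. Realised familywise error moves closer to 5% without exceeding it.
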